### Primary outcomes

#### Rated by participant (self-report)

Adult Barkley Current Symptoms Scale [30]The Barkley Current Symptoms Scale includes questions that assess the frequency of the 18 DSM–IV symptoms for ADHD. Items assess the frequency of 9 inattentive and 9 hyperactive/impulsive symptoms on a scale ranging from 0 = “never or rarely” to 3 = “often” with a score of 2 or above indicating the presence of a symptom. The presence of six or more symptoms for each subtype is considered clinically significant, in line with the recommended threshold of six out of nine symptoms in DSM- IV. This measure has strong reliability and validity and has been widely used in ADHD research.Work and Social Adjustment Scale [31]This is a reliable and valid measure [32] that has been used widely to assess impairment in functioning in relation to an identified problem. It consists of 5 questions each rated on an 8-point scale (0 = “not at all impaired” and 8 = “very severely impaired”). A higher score indicates higher impairment.

### Secondary outcomes

#### Rated by participant (self-report)

3.Clinical Outcomes in Routine Evaluation Outcome measure (CORE-OM) [33]. This is a 34-item generic measure of psychological distress and is one of the most widely used outcomes for psychological therapies in primary and secondary care in the UK [34]. It has been shown to correlate well with other measures of psychological distress in an aggregated clinical sample and cut-off scores for determining clinical significance are available.4.Hospital Anxiety and Depression Scale (HADS) [35]This is a 14-item scale with two subscales measuring anxiety and depression respectively. It has been found to reliably and validly assess the symptom severity and caseness of anxiety disorders and depression in psychiatric and primary care patients and in the general population [36].5.ADHD Cognitions Questionnaire Participants will rate various beliefs in relation to their ADHD. The reliability and validity of this scale is being evaluated in a parallel study.6.ADHD Behaviours Questionnaire Participants will rate the extent to which they engage in certain behaviours in relation to their ADHD. The reliability and validity of this scale is also being evaluated in a parallel study.7.The Rosenberg Self-Esteem Scale [37].This is a 10-item uni-dimensional measure of global self esteem, self-worth or acceptance that has been shown to be reliable and valid including in psychiatric outpatients [38].8.The Autism Spectrum Quotient [39] *†This is a 50-item questionnaire designed to assess autism spectrum symptoms in the general population. Results so far show good reliability. Studies in adults show that the scale can distinguish between ASD and controls as well as between ASD and psychiatric conditions such as OCD and social anxiety [39-42]. The scale’s ability to distinguish ASD from ADHD is, however, limited [43]. The scale is therefore only used as a screening tool in conjunction with the clinical assessment and the initial research assessment interview in assessing the presence of a possible autistic spectrum disorder. To the authors’ knowledge no alternative self-report scale of autistic spectrum disorder symptoms is available.9.Global Impression scales (improvement** and satisfaction**) (adapted from Guy 1976 and used previously in Deale et al. 1997; [44,45]) provide self-rated global measures of improvement and treatment satisfaction on a seven point scale. Improvement is rated on a scale from 1 = “very much better” to 7 = “very much worse”; satisfaction is rated on a scale from 1 = “very satisfied” to 7 = “very dissatisfied”.10.Frost Multidimensional Perfectionism Scale, Unhealthy Perfectionism subscale [46], The original scale had 35 items, however a subsequent factor analysis revealed two ‘higher order’ factors, interpreted as Healthy (Organisation and Personal standards;13 items) and Unhealthy perfectionism (Doubts about actions, Concerns over mistakes, Parental criticism, Parental expectations; 22 items) [47,48]. Responses are rated on 5-point Likert scale where 1 = “strongly disagree” and 5 = “strongly agree” and a higher score indicates greater perfectionism.11.Beliefs about Emotions Questionnaire [49]This is a 12-item scale that assesses beliefs about experiencing or expressing negative thoughts and emotions. It was validated using participants with chronic fatigue syndrome and healthy controls and shows good internal reliability, validity and sensitivity to change. Responses are rated on a seven point Likert scale where 6 = “totally agree” and 0 = “Totally disagree”.

#### Nominated informant ratings

12.Adult Barkley Current Symptoms Scale – Other Report Form. This is an informant version of the Adult Barkley Current Symptoms Scale.13.Global Impression Scales (improvement)**. Global measure of improvement (see 9) rated by the nominated informant.

#### Independent evaluator ratings

14.Global Impression scales (severity and improvement)**. Global measures of severity and improvement (See 9) rated by the independent evaluator.15.Global Assessment of Functioning [50]. A generic rather than diagnosis-specific scoring system of psychological, social and occupational functioning and covers the range of positive mental health to severe psychopathology. For this study it will be used to provide a single score of functioning. While questions have been raised as to its utility for individual patients, it appears to have acceptable reliability at the group level [51].16.The independent evaluator will also be asked to say which group they thought the participant was in and why (possible responses are “guess”, “the participant told me” and “other, please state”).

### Therapist ratings

17.Ratings of CBT compliance and adherence**. Number of CBT sessions attended, whether they were face-to-face or telephone, their duration and percentage completion of homework will be recorded. At the end of CBT treatment, the therapist will also score how well the participant adhered to the CBT approach, the extent to which the participant accepted the model of therapy and the therapeutic alliance on a five-point scale ranging from “not at all” to “completely”. They will also rate homework compliance on a scale of 0% to 100% completion on a session-by-session basis. These measures were adapted from a previous RCT [52]. A new measure was developed for the current study whereby the therapist will also rate their impression of the strength of the therapeutic alliance on seven point scale from 1 = “poor” to 7 = “excellent”.18.Global Impression scales (severity and improvement) ** Global measures of severity and improvement rated by the therapist (See 9). For practical reasons these will be administered in the CBT condition only.

### Other

19.Medications and doses. At the each assessment point the assistant psychologist will take a record of current medications and doses, any changes, compliance with medication. They will also ask about any adverse events/reactions that may not yet have come to the attention of the trial personnel.20.The details of TAU for all participants i.e. number of sessions with the service managing their ADHD (the Maudsley Adult ADHD Service or their local service) will be recorded.* baseline only.** 30 weeks and 42 weeks only.† This is routinely administered during clinic assessments. This will only be included in the questionnaire pack if, for any reason, it has not already been completed.

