**Methods/design:**

Sixty patients with a diagnosis of adult ADHD attending a specialist clinic are randomly allocated to 1 of 2 treatments, ‘Treatment as Usual’ (TAU) or TAU plus 16 sessions individual CBT (TAU + CBT). In the TAU + CBT, the first 15 sessions take place over 30 weeks with a 16th ‘follow-up’ session at 42 weeks. Outcomes are assessed at 30 weeks and 42 weeks following randomization. The two primary outcomes are self-rated ADHD symptoms and functioning (occupational and social). Secondary outcomes include distress, mood, ADHD-related cognitions, ADHD-related behaviours and informant-rated ADHD symptoms.

The primary analysis will include all participants for whom data is available and will use longitudinal regression models to compare treatments. Secondary outcomes will be analysed similarly.

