### Randomized treatments

#### Treatment as usual

All participants in the trial will receive TAU. This will include visits to their clinic doctor in the Service, if they have one, or visits to their local Specialist ADHD Service, CMHT or GP for management of their ADHD. They may be given some general advice but no specific advice with regard to strategies they may use to manage their ADHD symptoms. There will be no additional therapist involvement. The number of outpatient sessions will be recorded along with any treatments given to participants by the clinic doctor.

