### CBT

In addition to treatment as usual, participants will also attend up to 15 weekly 50-minute CBT sessions over a period of 30 weeks as well as their treatment as usual sessions at the clinic. They will have a sixteenth, follow-up CBT session at 42 weeks.

During the early stages of treatment a shared formulation will be derived by patient and therapist. In the formulation links will be made between the individual’s predisposition, their early life experiences and current behavioural coping and cognitions. Treatment will then focus on the problematic cognitions and behaviours identified in the assessment and agreed in the formulation, while drawing on a range of evidence-based strategies such as thought records and behavioural experiments. Therapists will also have access to a range of skills-based approaches as have been used in previous studies, as and when they are indicated by the formulation (e.g. time management). A CBT manual has been developed but will be updated iteratively.

The aim will be to complete up to 15 sessions within 30 weeks. These will be scheduled approximately weekly several weeks ahead. If the patient is not able to attend an appointment because of ill health, the appointment will be rescheduled to within one week’s time. If it is not possible to rearrange the session within this timeframe, a session may be held over the phone. Ideally no more than three sessions in a row should take place over the phone. However if the choice is between not having a session and offering a telephone session, a telephone session will always be offered, even if three consecutive phone sessions have already taken place.

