### Independent overseers

There will be a combined Trial Steering Committee (TSC) and Data monitoring and ethics committee (DMEC). They will be responsible for monitoring progress of the trial and serious adverse events or reactions. A trial management group will meet more regularly to discuss the day-to-day running and management of the trial. The combined TSC and DMEC will aim to meet at least three times over the course of the trial.

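### The catch-up question on adverse events risks unequal ascertainment between arms, because CBT participants have up to 15 extra therapist contacts before week 30 and TAU participants have none

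*Protocol article*

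**What the plan says.** The enquiry about harms is described under *Other*, attached to the medication record. On timing: "At the each assessment point the assistant psychologist will take a record of current medications and doses, any changes, compliance with medication". On adverse events: "They will also ask about any adverse events/reactions that may not yet have come to the attention of the trial personnel". Neither sentence is limited to one arm. On follow-up times, the abstract says: "Outcomes are assessed at 30 weeks and 42 weeks following randomization". Table 1 adds columns for treatment and trial discontinuation and does not tie them to an arm.

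Contact between assessments differs by design. Under *CBT*, "participants will also attend up to 15 weekly 50-minute CBT sessions over a period of 30 weeks", with a sixteenth session at 42 weeks. The same section shows that therapists may hear of illness: "If the patient is not able to attend an appointment because of ill health, the appointment will be rescheduled to within one week’s time". Under *Treatment as usual*: "There will be no additional therapist involvement". Usual care is given to all participants, and its description begins: "This will include visits to their clinic doctor in the Service, if they have one". Otherwise it comes from a local specialist service, a community team or a general practitioner.

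Under *Assessments*, the protocol states that the assistant psychologist will not be kept blind. Under *Independent overseers*, it says of the combined committee: "They will be responsible for monitoring progress of the trial and serious adverse events or reactions".

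**The concern.** The scheduled question tops up what is already known; it does not ask for a full account of the interval. The record therefore has two sources. One is whatever reached trial staff between assessments, and the other is what the participant adds when asked. The second source is nominally the same in both arms. The first is not, because a CBT participant may speak to a trial therapist up to 15 times before week 30 and a TAU participant has no such contact.

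If therapists pass on some of what they hear, equal true harm would appear as more recorded events on CBT. Worsening under TAU would be the harm most easily missed. With 30 participants per arm planned, event counts may be small, and a few events noted only through therapy could shape how the harms table is read. An asker who knows the allocation adds a further source of difference, whose direction cannot be predicted.

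**Working it through.** The protocol gives no adverse event rate and no detection rate, so there is no figure of its own to reproduce on this point. The sample size of 23 per group is not an input.

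**Inputs from the document**
- Enquiry at each assessment, both arms, aimed at events not yet known (*Other*).
- Scheduled post-baseline assessments at 30 and 42 weeks. The recall intervals are 30 weeks and then 42 − 30 = 12 weeks.
- Extra therapist contacts before week 30: up to 15 for CBT (*CBT*), 0 for TAU (*Treatment as usual*).

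**Assumptions (not in the document)**
- True event rates are equal in the two arms.
- d = probability that an event would be picked up by the scheduled enquiry, the same in both arms.
- s = probability that an event becomes known through a CBT session and is recorded.
- The two routes act independently.

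**Recorded totals.** TAU records a share d of events. CBT records 1 − (1 − d)(1 − s). The ratio is

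[1 − (1 − d)(1 − s)] / d = 1 + s(1 − d)/d.

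| d | s = 0 | s = 0.2 | s = 0.5 | s = 0.8 |
|---|---|---|---|---|
| 0.5 | 1.00 | 1.20 | 1.50 | 1.80 |
| 0.7 | 1.00 | 1.09 | 1.21 | 1.34 |
| 0.9 | 1.00 | 1.02 | 1.06 | 1.09 |
| 1.0 | 1.00 | 1.00 | 1.00 | 1.00 |

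For example, with d = 0.5 and s = 0.8: [1 − 0.5 × 0.2]/0.5 = 0.90/0.5 = 1.80.

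**A route shared by both arms.** Suppose usual-care contact brings an event to notice with probability c in either arm. Then d is replaced by 1 − (1 − d)(1 − c). With d = 0.5 and c = 0.4 this is 1 − 0.5 × 0.6 = 0.70. With s = 0.4 the ratio is (1 − 0.30 × 0.6)/0.70 = 0.82/0.70 = 1.17. With s = 0.8 it is (1 − 0.30 × 0.2)/0.70 = 0.94/0.70 = 1.34. A shared route shrinks the gap but does not close it.

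**Newly elicited events alone are no remedy under the present wording.** If events already known are not asked about again, the CBT arm yields d(1 − s) newly elicited events against d in TAU, a ratio of 1 − s. For s from 0.2 to 0.8 that is 0.8 down to 0.2, a distortion the other way. The question itself has to cover all events before the arms can be compared on it.

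**The case against.** The strongest case against is that this is one sentence in a condensed article, and that a catch-up question helps the arm with less contact by giving it a route to report. Several parts of that case stand.

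- A reader might infer that known events are left out, or that the question is put to one arm only. The text supports neither: the question is put in both arms and adds to what is known.
- A reader might infer that only CBT participants meet trial personnel before week 30. The document does not say so. The term is undefined, and participants in either arm may see a doctor in the same Service.
- A reader might take the discontinuation assessment as an extra visit for CBT. *Assessments* describes bringing outcome assessment forward, and Table 1 does not restrict it by arm.
- No therapist record of adverse events is described. *Therapist ratings* lists attendance, homework, adherence, alliance and global impressions. If therapists pass nothing on, s = 0 and the ratio is 1.
- No between-arm test of harms is described, and a fuller procedure may exist in documents not shown. Its absence from the article is not a fault.
- The committee's remit is serious events, which may be the least likely to be forgotten. It cannot be assumed that its view would be distorted to the same degree.

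These points limit the claim but do not remove it. Clinic-doctor contact belongs to usual care, which both arms receive, so therapist contact comes on top of it. The *Discussion* concedes that therapist time is unmatched, but in relation to whether effects are specific to CBT, not to harms. And the point concerns a rule that the article states, not one that it omits.

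**Conclusion.** The point holds as a risk of unequal ascertainment, not as a demonstrated bias. The stated enquiry adds to events already known, and CBT participants have up to 15 more occasions before week 30 on which an event can become known. Any comparison of recorded harms by arm could therefore overstate the CBT count.

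Under equal true harm the illustrative recorded ratio is 1.0 to 1.8. This rests on assumed detection rates, on the scheduled enquiry working equally well in both arms, and on independence of the two routes. It is exactly 1.0 if scheduled recall is complete or if therapists pass nothing on. The document settles neither condition. The primary and secondary efficacy outcomes are not affected.

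**What to change.** Replace the catch-up wording. At 30 and 42 weeks, and at any discontinuation assessment, ask every participant in both arms the same scripted question about all adverse events since the last scheduled assessment, whether or not already known. Record the source of each event: scheduled question, therapy session or other route. An event reported by more than one route should carry each source.

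Base any between-arm comparison on events elicited by the scheduled question. List separately the events that surfaced in therapy or by other routes. All events, whatever their source, still go to the oversight committee.

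Optionally, tabulate by arm the number rated worse on the independent assessor's global improvement scale, which Table 1 already schedules at 30 and 42 weeks.

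The cost is a few minutes per assessment, some repetition of known events, one form field and one extra listing. The change does not make the asker blind; a fixed script only limits the room for that to matter.

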### Ethics approval

The trial will be conducted in compliance with ethical approval (City Road and Hampstead Research Ethics Committee; reference 09/H0721/49) and R&D approval (reference R&D2009/051).

The study opened to recruitment February 2010.

### Sponsor

The main Sponsor is South London and Maudsley NHS Foundation Trust.

### Independent overseers

There will be a combined Trial Steering Committee (TSC) and Data monitoring and ethics committee (DMEC). They will be responsible for monitoring progress of the trial and serious adverse events or reactions. A trial management group will meet more regularly to discuss the day-to-day running and management of the trial. The combined TSC and DMEC will aim to meet at least three times over the course of the trial.

### Therapists’ compliance with treatment manual

Therapists’ compliance with treatment manuals will be monitored in two ways. All therapists will receive a minimum of monthly face to face group supervision sessions. All sessions will be audio-recorded and some recordings will be used to provide feedback to therapists on competence and treatment fidelity. Although the patient manual will be developed iteratively, the broad approach and content of therapy will be agreed by the principal investigator and the clinicians involved in the study ([name]) at the outset of the trial. Deviations from this will be noted and feedback given to the therapist. Following completion of the treatment sessions and of the patient and therapist manuals, 10% recorded sessions will be rated by two independent raters in order to assess adherence to the manual-defined therapy.

### Analyses

#### Sample size

The following power analysis is based on a previous study by Safren et al. [24] which compared CBT plus continued medication with continued medication only in ADHD and used the same primary outcome symptom measure as will be used in the current study.

A sample size of 23 in each group will have 90% power to detect a difference in means of 9.000. This is the difference between the change score of the Group 1 mean of 14.200 (SD = 7.2 assuming a correlation between pre and post measure of r = 0.5) and the Group 2 mean of 5.200 (SD = 9.05, assuming a correlation between pre and post of r = 0.5). This is also assuming that the common standard deviation is 9.050 (conservative estimate) using a two group *t*-test with a 0.050 two-sided significance level.

The intention to treat number is 23, however we will try to recruit 30 to each group to allow for dropouts.

#### Analysis plan

Between group effect sizes will be computed for the outcome measures.The two conditions i) CBT and ii) TAU will be compared using random effects modelling. Intention to treat analysis will be used. It is predicted that the CBT group, covarying for baseline levels, will have better results than the TAU group on the primary outcome (i.e. lower score on self-rated ADHD symptoms and scores indicating higher levels of social and occupational functioning) and secondary outcome measures. A more detailed analytic structure will be written before data analysis begins.

## Discussion

This is a randomized controlled trial to further investigate the feasibility and acceptability of CBT in addition to TAU as compared with TAU alone. This is the first study to investigate individualized formulation-based CBT for adults with ADHD using a randomized controlled design. It is hoped it will provide important information about the efficacy of this approach in this client group. It will also provide information as to the feasibility of conducting a larger better-powered study in the future, potential effect sizes and acceptability of the approach to patients. Finally it will provide some preliminary information about mechanisms of change as well as predictors of successful CBT outcome.

A limitation of this study is that it is not designed to match for therapist time and attention and so it will not be possible to say whether any changes seen in the CBT group are specific to the CBT. Future studies should evaluate this formulation-based approach alongside an active control condition.

It is hoped this study will provide further information for people with ADHD, healthcare providers and commissioners as to which treatments are most useful for ADHD in adulthood. It will also provide some preliminary information about the mechanisms of change and predictors of outcome in terms of symptoms and functioning.
